## Background

**Scope of Problem.** Suicide and suicidal behavior (SB) during adolescence has been increasing over the past two decades. Suicide is the second leading cause of death among adolescents in the U.S., with the CDC reporting in 2017 that 17.3% of deaths in youths ages 10-24 were due to suicide (1). The trend is particularly alarming for girls who have experienced a three-fold increase in suicide deaths since 1999 (2). Data from high school students completing the Youth Risk Behavior Surveillance Survey show an increase in the suicide attempt rate as well, from 6.3% in 2009 to 8.6% in 2015 (3).

Accordingly, hospital encounters for suicidal adolescents have doubled in the past decade (4). The period following discharge from a psychiatric hospitalization is a time of increased risk for suicidal behavior (5-7) including suicide deaths (8). Our own prospective follow-up studies found 19% and 20% suicide re-attempt rates by 6 months post-discharge (9, 10). Inpatient populations are also at risk of treatment disengagement from outpatient services, either through a lapse in the continuity of care or treatment non-adherence (11). High re-admission rates ranging from 30-50% within 30 days of hospitalization have been reported (12, 13). Thus, intervention efforts that focus on the period immediately following hospitalization may efficiently reach the highest-risk adolescents, at the highest-risk time, and reduce healthcare costs incurred by re-admissions.

**Current Psychosocial Interventions.** Psychosocial interventions for suicidal behavior mostly target symptoms of psychiatric illness, often using a cognitive-behavioral therapy (CBT) framework. However, results from two meta-analyses indicate a lack of efficacy in suicide interventions for adolescents (14, 15). One meta-analysis of CBT to reduce SB identified 6 adolescent and 18 adult studies and found that a significant treatment effect was observed for adult samples but *not* for adolescents (15). A more recent meta-analyses which included 9 adolescent studies similarly found that psychotherapy reduced suicide attempts in high-risk adults but not adolescents (14). The study that showed the strongest effect in this meta-analyses, was designed for youth with comorbid substance use and suicidality and conducted by our group (16). Unfortunately, a larger trial of this same intervention, which did not require youth report substance use, did not yield significant between-group effects on suicide related outcomes (10). One recently published study not represented in these meta-analyses is a multisite DBT study of 173 adolescents (17), which found advantages of Dialectical Behavior Therapy (DBT) over the comparison group at the end of the 6 month treatment period but not at the 12-month f/u on SA. This study, although promising, was highly intensive, as have been almost all studies to date*.* The majority of studies reviewed here and represented in the meta-analyses, primarily focus on crisis intervention, psychiatric symptomatology, regulating negative affect, and reducing cognitive distortions. Alternative approaches to reducing suicidal behaviors, particularly in adolescents, are warranted.

**Low Positive Affect (PA).** Our pilot work and other recent data suggest the importance of considering how low PA contributes to suicide risk. In a study of psychiatrically hospitalized suicidal adolescents conducted by the MPIs, low PA prospectively predicted time to suicidal events, i.e., either a suicide attempt or an emergency intervention for an acute suicidal crisis, in adolescents over 6 months of f/u. This effect remained significant after controlling for a number of other predictors, including depression severity and anhedonia (Hazard Ratio = 1.82; p<.05) (9). In a cross-sectional study of over 1000 adolescents, gratitude was inversely associated with suicidal ideation (SI) and suicide attempts (18). The effect of PA on SI has also been demonstrated in older patients. In a study of 462 primary care patients, age 65 and over, PA distinguished suicide ideators from non-ideators, after controlling for age, gender, depression, negative affect (NA), illness burden, activity, sociability, cognitive functioning and physical functioning (19). These studies suggest that low PA is a risk factor for SB independent of negative affect (NA) and may be another mechanism that leads to SB.

The *Broaden and Build theory* offers a clear conceptual model for the association between PA and SB. This model asserts that one function of PA may be to broaden attentional scope to help individuals be more open to novel stimuli and social supports, which in turn, broadens and builds psychological and social resources necessary for survival (20-25). PA has been shown to broaden attentional scope (21), motivate thought-action tendencies (i.e. increase behavioral activation) (20), and counter the deleterious effects of negative emotions (26). Drs. Fredrickson and Joiner examined the reciprocity of influence between PA and “broad-minded coping” measured by items such as “think of different ways to deal with the problem,” and “try to step back from the situation and be more effective” (23). They assessed positive and negative emotions at two time points 5 weeks apart and found that those who experienced more positive emotions had higher increases in broad-minded coping. In turn these skills predicted increased positive emotions over time.

Most individuals, particularly those who are depressed, process emotions through a negativity bias (27), in which individuals pay more attention to and react more strongly to negative stimuli than positive stimuli; thus, it is likely that positive affect and experiences are frequently being discounted. Understanding the functions of PA and NA, and intentionally bringing greater attention and awareness to PA, may be an important counterweight to this negativity bias, and in turn, may be mechanism reducing suicide risk.

**Positive Psychology Interventions (PPI).** Few PPIs have specifically been applied to patients with suicidal behavior. Two meta-analyses of PPI for depression and well-being found that these interventions have small to moderate effects in enhancing well-being and decreasing depressive symptoms and that effects are stronger for individual vs. group formats (28, 29). However, the vast majority of these interventions were with nonclinical populations, with nearly half of them conducted with college students. Only a handful of studies recruited from clinical or hospital settings (30-33). The few studies conducted with suicidal populations (not included in the meta-analyses) have yielded mixed findings. One recent study of 201 inpatient adults randomized to a 7-day program of either gratitude or food diary found significant between group differences on SI, psychological pain, hopelessness and optimism, favoring those in the gratitude condition (34). However, another study, in which 65 adult inpatients were randomized to a positive psychology exercise (e.g., gratitude letter) vs. a cognition-focused intervention (e.g., recalling daily events), found that contrary to the hypothesis, those randomized to the cognition-focused intervention had significantly greater improvement in depression, SI, optimism, and gratitude, compared to the positive psychology intervention (35). No PPIs for suicidal adolescents, to our knowledge, have been published with the exception of our pilot work.

**Rigor of the Prior Research.** As noted above, although a number of interventions for adolescent suicidal behavior have been tested, they focus on negative affect and the findings to date are modest. New approaches are indicated.

**Skills to Enhance Positivity (STEP).** We developed the STEP intervention for adolescents admitted to an inpatient psychiatric unit due to suicide risk. STEP is a multi-modal, adjunctive intervention involving 4 individual sessions delivered on the inpatient unit, followed by text or email messaging post-discharge to assess mood and “push” positive affect strategies for up to three months. While STEP borrows heavily from preceding positive psychology interventions, such as Seligman’s positive psychotherapy (PPT) (32), importantly, it is also distinct. STEP does not address happiness, optimism, or meaning, which may feel unattainable or invalidating to patients in acute distress. Rather, it focuses on increasing attention and awareness to positive emotions and experiences that may be easily discounted by the cognitive constriction that often accompanies SI and SB. Consequently, specific exercises designed to increase attentional awareness (i.e., psychoeducation on functions of emotions, mindfulness, gratitude, and savoring) are practiced, and, in this sense, STEP more closely aligns with acceptance-based approaches to treating depression, which have become increasingly common (36).

MPIs [name] and [name] have conducted an open trial (N = 20) (37) and a pilot RCT (N = 52) (MH R34101272) (38) of STEP; both trials indicated excellent feasibility. The samples were characteristic of inpatient settings, i.e., high rates of comorbidity, especially mood disorders (92%), NSSI (96%), and past SA 52%). (See 43, 44 for details). We will recruit participants from the same site, thus anticipate the same clinical features in the proposed study. On average, 81% of in-person sessions were completed in the open trial, and 83% in the RCT. Participants responded to the text-messaging component of STEP on 74% of days in the open trial and 70% of days in the RCT. Based on feedback received from the open trial in which respondents requested text messaging be extended, we offered an optional 3-month extension of texts 3x/week to those randomized to STEP in the RCT; 52% opted for this extension without any financial incentives. Acceptability ratings for in-person sessions and text messaging, as well as the specific exercises introduced in STEP, were high for both adolescents and parents in both trials, with 95% in Open and 88% in RCT rating quality of services as either good or excellent.

In the RCT, over 6 months of f/u, 5 of 26 participants in the STEP condition (19%) vs. 10 of 26 in the Enhanced Treatment as Usual (ETAU; healthy habits texts) condition (38%) had a suicidal event. Six suicidal events were reported among STEP participants and 13 events were reported among ETAU participants. Thus, those randomized to STEP had 50% fewer events and 50% fewer participants engaging in suicidal events, compared to ETAU. This frequency count corresponds to a medium to large effect size *h* of .43. Furthermore, those in the STEP condition saw a more dramatic decrease in active SI from baseline compared to their worst week during the f/u period (STEP 49% vs. ETAU 19% decrease) (Fig 1). At baseline, 80% of STEP participants and 69% of ETAU participants reported active SI in the week preceding hospitalization. The percentages of those with active SI during their worst week of follow-up (f/u), dropped to 32% in STEP vs. 50% in ETAU (Cohen’s d = -0.74). Compared to ETAU, STEP had significantly greater improvement in depression (parent report on the Beck Depression Inventory)(39) at post-treatment (d=0.76; 95% CI 0.21-1.30) (38).

Our data also suggest that STEP engaged the target of PA. On the attentional dot probe task using words, groups did not differ at baseline or post treatment. However, a significant between group difference was found with those in the STEP condition showing more attention biased toward happy words at the 3-month f/u compared to the ETAU group, *t*(34) = 2.06, *p* = .048, η^2^ = .04. While our self-report assessments did not yield any significant between-group differences, stronger pre-post effects (from baseline to post-tx, and baseline to f/u) were observed in STEP on *gratitude* and *satisfaction with life*, with significant within group comparisons observed in STEP but not in ETAU for 3 out of 4 comparisons (effects sizes (Cohen’s *d*) ranging between 0.59-0.87). Furthermore, mood responses based on the six Modified Differential Emotions Scale (mDES)(25) items delivered daily to STEP participants, suggested that in 400 total days of full reporting (58% of surveyed days), 84% of STEP participants reported more days in which their PA > NA. We also observed a strong within-group effect on our secondary mechanism of negative affect for those in STEP (d = 1.01), although there was no statistically significant difference between groups. Finally, we have data supporting our hypothesized mechanisms are related to suicide outcomes. *Satisfaction with Life* at post-treatment predicted SE and active SI at the 6 month f/u, and these measures at the 3 month f/u, predicted SE at 6 month f/u. Adjusting for direction of effects, odds ratio (*OR)* ranged from 1.10 to 1.17; p = .04 to .003, respectively. Furthermore, PA (mDES) at 3 month f/u predicted 6 month active SI (adjusted OR = 2.33; p = .03), and NA (mDES) at post-treatment and 3 month f/u predicted 6 month SE and active SI (OR ranged from 2.69 to 4.94; p = .02 to .004).

These preliminary data importantly demonstrate the feasibility, and our capability, of mounting a large-scale trial and implementation study of the STEP intervention. We have the capacity to recruit adolescents, and to engage them in STEP. We also show evidence of efficacy and engagement with the target, although we recognize that the small sample size of the pilot trials leads to low precision of these effect size estimates.

**Significance.** As rates of suicide and suicidal behavior are on the rise in adolescents, our proposal has public health significance by targeting a high-risk, vulnerable, adolescent population during a time of acute need (Healthy People 2020 Objective MHMD HP 2020- 2: Reduce suicide attempts by adolescents). This application also strongly aligns with the NIMH 2020 Strategic Plan for Research, specifically objective 3.3. “test interventions for effectiveness in community practice settings” and 3.3.c “enhancing the practical relevance of effectiveness research via deployment-focused hybrid effectiveness-implementation studies,” as well as objective 8.4 of the National Strategy for Suicide Prevention to promote continuing care after hospital usage which in turn may reduce re-hospitalization, another significant cost containment and public health benefit. Our proposed adjunctive intervention is also clinically significant and innovative because it was developed to work synergistically with psychotherapies and designed such that it can be delivered either adjunctively or integrated as a module into another manualized protocol. The integration of remote reminders facilitates daily in-vivo practice of skills. We will be able to explore potential moderators that may inform which youth benefit from this treatment approach, with attention to biological sex and gender identity, severity of depressed mood, service level factors, (i.e., number of sessions received, engagement with the program) and fidelity of frontline staff to the delivery of STEP (40). Finally, **the rigor of the proposed research** is evident in the strong scientific premise as it is based on the research literature, including our own prospective naturalistic study, an open trial, and a pilot RCT. Furthermore, we gather data from multiple sources (participants, parents, staff), and propose multiple assessment modalities (clinical interviews, explicit self-report measures, implicit behavioral tasks and eye tracking) to assess primary and secondary outcomes, and utilize quantitative and qualitative methods to address our exploratory aim regarding implementation. Our conceptual model is premised on the Broaden and Build theory of positive affect – a model that has garnered abundant empirical support in social psychology laboratories but has yet to be translated towards efforts to prevent suicidal behavior. Our findings could build support for an ancillary mechanism to suicidality and further inform the positive valence domain of RDoC.

## Risk/Benefit Assessment

### Known Potential Risks

1. Potential coercion: It is possible that patients may feel coerced into participating.
   1. The risk of potential coercion will be minimized by following standard procedures for obtaining informed consent, which includes a statement that participation is completely voluntary. We will fully explain the study procedures, risks, benefits and alternatives to all prospective participants and their parent(s). Also, patients who do not consent or who withdraw at any time will receive usual clinical treatment with no prejudice.
2. Confidentiality and loss of privacy: We will be collecting considerable information about the participant and their parent that may create some distress and could cause social and psychological risk if released inappropriately. Additionally, participants in the intervention condition will be corresponding with the study by text messaging through their personal phone. Emails and phone calls may also be used to schedule interviews.
   1. All research personnel will receive training in research ethics. All information will be treated as confidential material and will be available only to research and clinical staff trained to deal appropriately with sensitive clinical issues. All PHI will be stored in REDCap and will require a log-in. We will identify participant research data by numeric ID only (i.e. no identifying information on research data) and maintaining any records containing potentially identifying information separate from any research data. Paper files will be stored in locked file cabinets; computer data files will be available only to authorized personnel and will be password protected. No names, only identification codes, will be used in presenting data in lectures, seminars, and papers. Transfer of any data from or to Brown University (and any of the participating sites: Beth Israel Deaconess Medical Center, Boston Children’s Hospital, Butler Hospital, Bradley Hospital) will be performed by trained research staff and will comply with all HIPAA guidelines including the removal of any personal health information. Participant confidentiality will be breeched only to protect the safety and welfare of research participants and only in accordance with state and federal law.
   2. We will take steps to mitigate the loss of confidentiality and privacy with emails, text messages, and phone calls, by reviewing with the participant, good practices to ensure privacy during the consent process. These include logging out of their email account after use, setting up a passcode to their phone, and not checking messages when other people are around. Research personnel are instructed to never leave voice messages with confidential information. You will have to enter a password to receive the text messages.
3. Risk of adverse events during the study: It is possible that some patients will have an adverse event during the study, including subsequent suicidal ideation or behavior or other adverse events.
   1. Since the intervention being evaluated in this study is an adjunctive intervention, participation in the study will not prohibit involvement in any other type of treatment. All subjects will be allowed (and/or encouraged) to participate in whatever type or amount of treatment is thought to be clinically indicated for the patient. Thus, participation in the study will not cause any subject to be deprived of a clinically appropriate treatment.
   2. Participants may be pulled out of regular group or milieu programming for study intervention sessions.
   3. All subjects in the study will receive enhanced monitoring of their clinical condition. We will obtain release of information forms and will communicate with the patient’s clinician(s) if clinical deterioration occurs. All patients will be monitored at each assessment point with respect to suicidality. Patients in ETAU will be monitored for suicidality based on a clinician’s standard practice. All patients in the experimental protocol will be monitored at every session of the intervention protocol with regard to suicidality.
   4. We will have procedures in place to respond to adverse events if reported. Please refer to 8.2.
   5. All adverse and serious adverse events will be recorded and reported, as outlined in the table below.

| **Table 1. Reportable event timetable** | | |
| --- | --- | --- |
| **Reportable Event** | **When is Event Reported to the IRB and NIMH DSMB** | **Reported By** |
| IRB/ISM/DSMB/OHRP/FDA Suspensions or Terminations | Any suspension or termination of approval must include a statement of the reason(s) for the action and must be reported promptly to the NIMH PO within **3 business days of receipt.** | Regulatory or Monitoring Entity and Investigator |
| Deaths related to study participation | Deaths must be reported immediately (no later than within **5 business days)** of the principal investigator first learning of the death. | Investigator |
| Unexpected [Serious Adverse Events](http://www.hhs.gov/ohrp/policy/advevntguid.html#Q6) related to study participation* | Reported within **5 business days** of the study team becoming aware of the SAE | Investigator |
| [Unanticipated Problems Involving Risks to Subjects or Others](http://www.hhs.gov/ohrp/policy/advevntguid.html#Q1) | Reported to the NIMH and IRB within 5 **business days** of the investigator learning of the event. | Investigator |
| [Adverse Event](http://www.hhs.gov/ohrp/policy/advevntguid.html#AA) | \|  \| For all AEs and SAEs that are deemed expected and/or unrelated to the study, a summary should be submitted with each tri-annual DSMB report for SAEs, and annual progress report for AEs to the DSMB. The IRB will receive all of these reports annually. \| \| --- \| --- \| | Investigator |
| Protocol Deviations  Protocol Violations | \|  \| With the annual IRB progress report. \| \| --- \| --- \|   Annual IRB progress report and 3x per year to the DSMB. | Investigator |

Note: although NIH recommends 10 days, local IRB requests 5 days

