## Safety Assessments

We do an assessment of suicidal ideation and behavior at every assessment time-point as these are our study outcomes. We do not utilize any other safety assessments. If the adolescent endorses suicidal ideation with intent and/or plan within the prior 2 weeks on the C-SSRS, then the RA contacts the clinician who conducts the suicidality procedures described below (See Appendix for full details).

**What is the degree of suicide risk?** Determine the extent of suicidality by asking about ideation, method/plan, the presence of threats (e.g. suicide note) and actual behaviors. If they endorse suicidal ideation, determine the risk that patient will move from low to higher risk. If an attempt has already occurred, determine its nature and assess future risk.

What is your urge to harm yourself right now?

What is your intent to kill yourself right now?

How often do you think about suicide?

How well can you control your thinking about suicide right now?

How well can you control your emotions right now?

How well can you control your actions and behavior right now?

1. **Irrespective of intent, what is preferred method for suicide?** What is the lethality and where will the method occur. i.e., will the person be isolated or is there potential for discovery?
2. **Suicidal intent?** Ask specifically about whether the patient has a desire to die. If yes, consider the degree and type of motivation: actually wants to die, does not particularly want to die but rather wants to escape an intolerable situation or wants to communicate something, such as asking for help, getting attention, making someone feel sorry or change their mind.
3. **Use of alcohol and other drugs**
4. **How effective is the environment for keeping the patient safe?**
5. **Complete safety plan if person will remain in the community.** If assessment indicates an emergency evaluation is necessary, make a plan with the parent and arrangements for an ambulance to transport the youth to the ED.

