### Time Period and Frequency for Event Assessment and Follow-Up

The occurrence of an adverse event (AE) or serious adverse event (SAE) may come to the attention of study personnel during study visits: baseline, follow-up assessments as well as intervention sessions.

All AEs, will be captured on the appropriate case report form (CRF). Information to be collected includes event description, time of onset, clinician’s assessment of severity and expectedness, relationship to study procedures (assessed only by those with the training and authority to make a diagnosis), and time of resolution/stabilization of the event. All AEs occurring while on study will be documented appropriately regardless of relationship. All AEs will be followed to adequate resolution.

Any medical or psychiatric condition that is present at the time that the participant is screened will be considered as baseline and not reported as an AE.

Changes in the severity of an AE will be documented to allow an assessment of the duration of the event at each level of severity to be performed. Documentation of onset and duration of each episode will be maintained for AEs characterized as intermittent.

Study personnel will record events with start dates occurring any time after informed consent is obtained until 7 (for non-serious AEs) or 30 days (for SAEs) after the last day of study participation. At each study visit, the investigator will inquire about the occurrence of AE/SAEs since the last visit. Events will be followed for outcome information until resolution or stabilization.

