### Safety Oversight

Safety oversight will be under the direction of the NIMH Data and Safety Monitoring Board (DSMB) composed of individuals with the appropriate expertise, including expertise in suicide risk assessment and intervention development. In addition, the study will have a Safety Officer independent from the study conduct and free of conflict of interest. The Safety Officer will meet at least 3X per year to assess aggregate safety and efficacy data from each arm of the study; additional responsibilities are delineated in Section 8.3 regarding safety monitoring. The DSMB will operate under the rules of an approved charter that will be written and reviewed at the organizational meeting of the DSMB. Before the study begins, each data element that the DSMB needs to assess will be clearly defined. The DSMB will provide its input to NIMH.

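### Suicidality monitoring at STEP sessions is promised in the risk section but does not fit the safety section, and the STEP-only sessions can make early AE/SAE capture differ by arm

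*Protocol*

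**What the plan says.** **Known Potential Risks** starts with a rule for both arms: "All patients will be monitored at each assessment point with respect to suicidality". It then separates them. For the control arm, "Patients in ETAU will be monitored for suicidality based on a" clinician's usual practice. For STEP, "All patients in the experimental protocol will be monitored at every session of the intervention protocol with regard to suicidality". It sends the reader to 8.2 for the response to adverse events.

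**Safety Assessments (8.2)** says "We do an assessment of suicidal ideation and behavior at every assessment time-point as these are our study outcomes", and then "We do not utilize any other safety assessments". The response it describes begins when the adolescent endorses recent ideation with intent or plan on the C-SSRS, and the research assistant then calls in the clinician. An appendix with full details is cited but is not among the pages at hand.

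**Time Period and Frequency for Event Assessment and Follow-Up (8.3.3)** says that AEs and SAEs "may come to the attention of study personnel during study visits: baseline, follow-up assessments as well as intervention sessions". It adds: "At each study visit, the investigator will inquire about the occurrence of AE/SAEs since the last visit".

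**Safety Oversight (10.1.6)** has the Safety Officer meet at least three times a year "to assess aggregate safety and efficacy data from each arm of the study".

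Two other places bear on the point. Scientific Rationale for Study Design states that the assessments are identical in the two conditions. Table 2, which itemises the four STEP sessions, lists no suicidality check; the nearest items are the context of admission and reasons for living, both in Session 1.

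**The concern.** There are two linked problems.

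First, the risk section relies on session monitoring as a protection for STEP participants, but the safety section gives it no place. A reader cannot tell whether it is a study safety assessment or part of ordinary unit care. Nor can a reader tell what follows in the study if a participant voices suicidality in a session, because the only stated trigger depends on an instrument that is not given there.

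Second, sessions are named as a place where AEs and SAEs are found, and only one arm has them. If events are asked about more often in STEP in the first days, some may be recorded there that would go unrecorded in ETAU. The Safety Officer reads safety data by arm. The AE items listed in 8.3.3 (description, onset, severity, expectedness, relationship, resolution) do not include how the event came to light. A small early excess in STEP could then be either harm or extra asking, and the data would not show which.

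**Working it through.** The plan gives no figure on this point to reproduce. The check sets the passages side by side and counts contacts.

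**1. Monitoring of suicidality**

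| Place | STEP | ETAU |
| --- | --- | --- |
| Known Potential Risks | assessment points and every session | assessment points and clinician's usual practice |
| Safety Assessments (8.2) | assessment time-points only; no other safety assessments | same |
| Schedule of Activities (1.3), C-SSRS | baseline, 3, 6, 12 months | same |
| Table 2, session content | no check listed | no sessions |
| Scientific Rationale | same assessments as ETAU | same assessments as STEP |

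The first row does not fit the others as written.

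**2. Study contacts at which AEs can be collected**

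Inputs: 4 sessions in STEP only (Administration and/or Dosing); follow-ups at 3, 6 and 12 months in both arms (Schedule of Activities); one baseline in both arms. Section 8.3.3 counts sessions among study visits and requires AE inquiry at each visit.

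- After baseline: STEP 4 + 3 = 7; ETAU 0 + 3 = 3.
- Baseline to 3 months, inclusive: STEP 1 + 4 + 1 = 6; ETAU 1 + 0 + 1 = 2.
- Baseline to 12 months, inclusive: STEP 1 + 4 + 3 = 8; ETAU 1 + 0 + 3 = 4.

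The STEP counts are maxima: sessions may be compressed, and 83% of in-person sessions were completed in the pilot RCT (Background). The whole difference of 4 lies between baseline and the 3-month visit. Most of it falls in the inpatient stay, although in the pilot the last session was sometimes held after discharge.

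**3. Which events could be affected**

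Recorded events include self-injury without hospitalization (8.3.1) and suicidal behavior and psychiatric ED or inpatient visits (8.3.2). Admissions are also taken from medical records, without distinction by arm (Strategies for Recruitment and Retention). What remains open is mainly early events that lead to no new admission.

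**4. Can the size be computed?**

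Extra STEP reports = participants × sessions × y, where y is the share of sessions that bring out a reportable event that would otherwise never be recorded. With 216 randomized 1:1, 216 / 2 = 108 per arm.

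- Full completion: 108 × 4 = 432 sessions.
- At 83% completion: 432 × 0.83 ≈ 359 sessions.

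The protocol gives nothing on y. Purely as assumptions:

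| y (assumed) | 432 sessions | 359 sessions |
| --- | --- | --- |
| 0% | 0 | 0 |
| 1% | 4.3 | 3.6 |
| 5% | 21.6 | 18.0 |

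The answer runs from nothing to about 20 reports, and the assumed y determines it entirely. This shows that the size is unknown; it is not an estimate of bias.

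**The case against.** The case on the other side is substantial.

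- **Milder reading of 8.2.** The sentence ruling out other safety assessments follows directly on suicidality assessment, and can mean no other domains or instruments. Session monitoring would then be clinical care. This is a fair reading, but the protocol does not state it, and 8.2 would still give no trigger for something voiced in a session.
- **Recall.** AE inquiry covers the time since the last visit, and the follow-up C-SSRS covers the time since the last assessment. The 3-month visit therefore reaches back over the inpatient stay in both arms. Sessions may change when an event is recorded more than whether it is. This stands in large part; recall of minor early events after three months is the gap that is left.
- **Setting.** During the sessions both arms are psychiatric inpatients. STEP patients are taken out of other therapeutic activities so that total contact is not raised. Conditions present at screening are not AEs, and a new psychiatric admission is unlikely for someone already admitted. All of this shrinks the difference.
- **Consequences.** No between-arm AE test and no numerical stopping rule is stated. Suicidal behavior is an expected SAE, an independent Safety Officer judges relatedness and expectedness event by event, and the DSMB works under its own charter with data elements defined in advance.

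A reader might infer that STEP participants do not in fact receive the promised monitoring. The protocol does not support that: Table 2 outlines teaching content, and the treatment manual and safety appendix are not at hand. A reader might also infer that unequal capture would lead to suspension of the trial. The safeguards just listed make that speculative.

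**Conclusion.** The wording conflict is real, and so is the structural difference between the arms. Both are minor.

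Known Potential Risks does not agree with Safety Assessments, nor easily with the statement of identical assessments or with Table 2. The protocol must say whether session monitoring is a study safety assessment and which response procedure in 8.2 applies to it. Which clinical rule is right is not for this review.

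Early AE/SAE capture can differ by arm because STEP has up to 4 extra study contacts at which AEs are to be asked about. This rests on 8.3.3 being applied as written, with sessions counted as study visits. The effect concerns safety data only, and mainly early events without a new admission. Look-back and record audit offset part of it, and its size cannot be computed from the protocol.

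It would be wrong to carry this over to the primary suicidal-event endpoint. Both arms are assessed for it on one schedule by blind evaluators, and the record audit applies to both.

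**What to change.** 1. Reconcile Known Potential Risks, Scientific Rationale for Study Design, Table 2 and Safety Assessments: state whether suicidality monitoring at STEP sessions is a study safety assessment, and which procedure in 8.2 applies to it.
2. Add a source-of-report item to the AE form (session, scheduled assessment, hospital record, other). Table layout can be left to the SAP, but the SAP cannot restore a source that was never collected.
3. Keep every event, whatever its source, in the main by-arm AE/SAE tables and in all reporting to the Safety Officer, IRB and DSMB. Dropping session-reported events from the main comparison could hide harm: the section on discontinuing the intervention itself foresees unexpected adverse reactions to its content, and a session is where these may surface.
4. Add one supplementary by-arm table restricted to events collected at the common assessments (3, 6 and 12 months) and from hospital records, and list by date the events first reported at sessions.

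The cost is some protocol wording, one form field and one extra table. Sample size, visits and the primary analysis do not change.
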